### Measurements

Figure 2 provides a summary of the measurements collected.

#### Sociodemographic characteristics

Participants will be asked to self-report age, sex and ethnicity.

#### Medical history

Relevant medical history and all concomitant medication will be recorded and checked against the participants’ medical record. Participants will also be asked to self-report items required to determine cardiovascular risk score using QRISK2.^19^

#### Physical measurements

Height will be measured to the nearest 1 cm using stadiometers available in the practice. Weight will be recorded to the nearest 0.1 kg using an electronic scale (SC-240 MA, Tanita Japan), which will also record the proportion of body fat using bioelectrical impedance. Waist circumference will be measured in the horizontal plane at the upper border of the iliac crest at the end of expiration^20^ using a fibreglass non-stretch tape measure fitted with a tensioning device (Gulick II Tape Measure, Fitness Mart USA). Seated blood pressure will be measured in triplicate with 1 min between each measure. All physical measures are performed by assessors trained according to the study manual of procedures.

#### Fasting blood sample

A fasting venous blood sample will be collected (to be analysed for glucose, insulin, HbA1c, HDL and LDL cholesterol, triglycerides). When baseline/enrolment appointments are scheduled at times when it may be inappropriate to fast, participants will be asked to arrange for a fasting blood sample to be collected at an alternative appointment within 7 days of the enrolment visit and before the participant commences the allocated weight loss programme.

#### Questionnaires

Participants will be provided with a questionnaire booklet which they will be asked to complete and return to the trial team in a postage paid envelope provided. The questionnaire booklet contains the following measures:
*OWLQOL*: a weight-specific instrument intended to be used to assess obesity-specific symptoms and quality of life, general functional status and well-being, and person-specific preference measurement.^21^

*Quality of life*: EQ-5D will be used as a standardised validated instrument used for measuring general health status.^22^

*Programme adherence*: self-reported adherence to the allocated programme and methods participants are using to attempt to lose weight will be recorded by questionnaire.
*Programme feedback*: will be assessed using several 5-point Likert scales, including whether there is an aim to continue with the programme.
*OxFAB*: a questionnaire to assess personal strategies used by individuals for the purposes of weight loss.^18^

### Retention and withdrawal

We will seek to follow up all participants except those who expressly withdraw from the study. Participants who decide to withdraw from or discontinue the intervention allocated as part of the study will be asked to return for follow-up visits to collect outcome measures. To promote participant retention and complete follow-up, participants will be offered a £10 gift card for attending each of the 6-month and 12-month follow-up visits.

### Adverse events

AEs are of relevance in this trial because many practitioners feel these programmes are poorly tolerated and unsuitable for routine use in primary care. We will record AEs following Good Clinical Practice. All serious and non-serious AEs that occur during the first 12 weeks of the study or until the termination of the weight loss programme will be recorded in participants who initiate one of the weight loss interventions. We will also record all AEs that are presumed to be or known to be related to gallstones up to 6 months.

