During the first 12 weeks the participant will meet with their counsellor weekly. Patients will be asked to follow a programme based on using formula meal replacement products (soups, shakes and bars) and milk comprising 810 kcal/day (3389 kJ/day). For the first 8 weeks, patients will be advised to replace *all* their usual foods and drinks with four of the formula products daily: 750 mL of skimmed milk, 2.25 L of water or other non-calorific drinks and a fibre supplement (total diet replacement stage). During the first 2 weeks, the formula products will be limited to liquid products (soups and shakes), but from week 3 onwards participants will have the option to include meal replacement bars as part of the formula product allowance. After 8 weeks there will be a 4-week stepwise reduction in the use of formula meal replacement products and a gradual reintroduction of food-based meals. The weight maintenance phase from week 12 to 24 participants attend monthly appointments at 16, 20 and 24 weeks, during this phase participants are advised to consume only one formula product a day, with the remainder of the diet to consist   of self-selected food. This weight maintenance phase will include a recommendation to return to the total diet replacement stage for periods of up to 4 weeks if participants regain 1 kg or more than their weight measured at 12 weeks.

All consultations with counsellors and formula products will be provided to participants by their nominated counsellor and will be free of charge for the first 24 weeks, after which the intervention will end. Participants in both groups will be free to choose whether or not to continue with the programme, but at their own cost.

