#### Comparator

The comparator intervention will consist of the usual weight management programme provided by a member of the practice nurse team who has been trained to offer a weight loss programme. The trial will take place only in practices where this is routine care. Participants allocated to the usual care group will not be prevented from attending other weight management groups if they choose to do so, but no NHS referrals to these schemes will be offered during the trial. The practice nurse will give participants a copy of the booklet ‘So you want to lose weight … for good’.^17^ This 47-page booklet provides advice akin to a behavioural weight management programme. The aim is to produce a weight loss goal of 0.5–1 kg/week. It includes goal setting, advice on portion control and physical activity, other behavioural strategies, and monitoring and feedback on progress. Nurses will be asked to offer a programme for 12 weeks, at a frequency that is usually used in the practice (eg, weekly or biweekly).

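### Adverse event collection is limited to participants who start treatment and has an ambiguous window; on the most coherent reading it stops at 12 weeks and misses non-gallstone events during repeat diet replacement in weeks 12 to 24

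*Protocol article*

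**What the plan says.** Four places in the protocol article bear on this point.

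- **Adverse events** sets the window: "All serious and non-serious AEs that occur during the first 12 weeks of the study or until the termination of the weight loss programme". It also sets the population: these events "will be recorded in participants who initiate one of the weight loss interventions". One event type has its own window: "We will also record all AEs that are presumed to be or known to be related to gallstones up to 6 months".
- **Exploratory outcomes** lists adverse event reports to 12 weeks, glosses that time as the end of the weight loss intervention, and repeats the 6-month limit for gallstone-related events.
- **Low-energy total diet replacement** has consultations and products supplied "free of charge for the first 24 weeks, after which the intervention will end". Weeks 12 to 24 are called weight maintenance, and in that phase participants are advised to "return to the total diet replacement stage for periods of up to 4 weeks if participants regain 1 kg or more" relative to their 12-week weight.
- **Comparator** gives usual care a shorter course: "Nurses will be asked to offer a programme for 12 weeks".

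Participant flow labels weeks 1 to 12 the weight loss phase and schedules visits at 12 weeks, 6 months and 12 months after randomisation.

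**The concern.** The word "or" in the window joins two limits without saying whether the earlier or the later one governs. The second limit, termination of the programme, can mean week 12 (end of the weight loss phase), week 24 (end of the supplied programme) or the day an individual stops. Site staff could therefore close the record at different times while each following the text.

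The restriction to participants who start treatment applies to collection, not only to analysis. Events that were never collected cannot be recovered by a later choice of analysis set.

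This matters because the Introduction says the trial will test whether these programmes can be provided safely, including to patients with multimorbidity. The Adverse events section itself justifies recording on the ground that many practitioners doubt the programmes are tolerable in routine care. A period in which participants may go back to full diet replacement is one a reader would expect the harms data to cover.

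**Working it through.** The plan gives no expected adverse event figure to reproduce, and the sample size of 270 plays no part here. The check compares window lengths, using the week counts in the sections above.

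**Inputs.** Diet replacement programme supplied: 24 weeks. Weight loss phase within it: weeks 1 to 12, of which the first 8 are total diet replacement and the next 4 food reintroduction. Repeat replacement: possible in weeks 12 to 24. Comparator programme: 12 weeks. Gallstone window: 6 months in both arms.

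**Reading A: a fixed 12 weeks.** The windows are 12 and 12 weeks, ratio 12/12 = 1.0. Coverage of the supplied diet replacement programme is 12/24 = 50% by calendar time. Coverage of repeat replacement after week 12 is nil, except for gallstone-related events. Participant flow, Comparator and Exploratory outcomes all fit this reading best.

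**Reading B: the later of 12 weeks and programme end.** The windows are 24 and 12 weeks. At full participation the person-time ratio is 24/12 = 2.0, so equal event rates would give twice as many events in the diet replacement arm. For the proportion of participants with at least one event, assume the same constant weekly first-event risk r in both arms. The proportions are 1 − (1 − r)^24 and 1 − (1 − r)^12. The values of r are illustrative; the protocol gives none.

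| Assumed r per week | Diet replacement, 24 weeks | Usual care, 12 weeks | Ratio from window alone |
|---|---|---|---|
| 1% | 21.4% | 11.4% | 1.89 |
| 2% | 38.4% | 21.5% | 1.78 |
| 5% | 70.8% | 46.0% | 1.54 |

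**Reading C: the earlier of 12 weeks and the individual's stopping date.** A participant who stops at week s (s < 12) is observed for s weeks, and the remaining 12 − s weeks are lost. The window then depends on adherence. It is unequal between arms only if stopping differs between them, and the protocol gives no stopping rates.

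**Result.** A is equal but incomplete over the 24-week programme. B covers that programme but is unequal. C is at most 12 weeks and depends on stopping. No reading is both equal and complete.

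**Population.** Under all three readings the denominator is participants who started. The routes to starting differ: referral to a commercial counsellor, with a medication review for those on relevant drugs, against a programme run by the practice's own nurse team. Allocation is open. Starting could therefore differ by arm, but without initiation rates no size can be given.

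**The case against.** The case on the other side is substantial.

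- **The 12-week window is coherent.** The protocol separates weight loss (weeks 1 to 12) from maintenance (weeks 12 to 24), so ending adverse event reporting with the weight loss intervention need not clash with a 24-week supply. This stands: A is the best reading, and on it the windows are equal.
- **A reader might infer that the harms comparison is both incomplete and unequal.** The documents do not support that. A is incomplete but equal, B is the reverse, and only C could be both, if stopping differed by arm.
- **A reader might infer that no serious event during repeat replacement is counted.** That is too strong, since gallstone-related events are recorded to 6 months.
- **A reader might infer that events causing people to stop are lost.** They are not. Such an event occurs before or at stopping and falls inside even the shortest window; only later events are lost.
- **A starters-only set is a familiar safety convention and applies to both arms.** True, and it distorts the comparison only if starting differs. But the convention normally concerns analysis, and here it limits collection.
- **50% is calendar time, not risk.** The first 12 weeks contain all 8 weeks of scheduled total replacement, and how often participants return to it is unknown. This stands.
- **The full protocol may say more.** The article condenses it, invokes Good Clinical Practice, and reports that the Trial Steering Committee reviewed the suitability of the safety data. Fuller rules may exist. However, the article states window and population explicitly, for serious and non-serious events alike, so this is stated text and not an omission.

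**Conclusion.** The point holds in a limited form. The text does not fix one adverse event window. On its most coherent reading the window is 12 weeks in both arms: half the supplied diet replacement programme by calendar time, and none of any repeat replacement in weeks 12 to 24, gallstone-related events excepted. The 2:1 person-time imbalance arises only if the later limit governs and participation is full. The ratios of 1.54 to 1.89 rest further on assumed equal weekly risks of 5% down to 1%.

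The starters-only rule is a weakness of unknown size. It would be going too far to say that it has already made the harms comparison non-randomised, because that requires initiation to differ by arm and nothing in the document shows that it does.

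Adverse events are an exploratory outcome, so the primary analysis and the sample size are untouched. What is affected is the stated aim of testing safe provision. The change is a low-cost improvement, and it has to be made before the data are collected.

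**What to change.** Amend Adverse events and the matching line in Exploratory outcomes as follows.

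1. Record all serious and non-serious events in every randomised participant, from randomisation to one fixed time that is the same in both arms, whether or not the programme was started or stopped. The 6-month visit is the natural choice: it is already scheduled, comes after the 24-week supply ends, and already closes the gallstone window. Retention and withdrawal already asks those who discontinue to attend follow-up.
2. Report by randomised arm. A set restricted to those who started may be shown as well.
3. Reconcile both sections with Low-energy total diet replacement on when the intervention ends, using separate terms for the end of the weight loss phase and the end of the supplied programme.

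The cost is a wording change, adverse event questions at an existing visit, more forms, and some recall error over the interval between the 12-week and 6-month visits (about 26 − 12 = 14 weeks, taking 6 months as 26 weeks).

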### Participant flow

The baseline/eligibility assessment will be scheduled with a practice nurse or healthcare assistant at their own GP practice, where informed consent for participation in the study will be obtained before eligibility will be formally assessed. After demographic information and all baseline measurements have been collected, the participant will be randomised to the allocated treatment group using the online randomisation system. The patients’ own GP will be notified by letter of the enrolment and randomisation of their patient, so that it may be documented on their medical record. Participants allocated to the low-energy total diet replacement programme and taking medications for type 2 diabetes, hypertension or high cholesterol will have their medications reviewed by a prescribing member of the clinical care team, usually the GP or trained nurse prescriber. During this medication review, the clinician will decide what changes to medications are required at the time the participant commences the low-energy total diet replacement programme, with guidance provided by the study team (see online supplementary figure 1). In addition, participants randomised to the low-energy total diet replacement group and who take antihypertensive medications will be provided with a home blood pressure monitor and asked to record blood pressure once daily during the weight loss phase (weeks 1–12). These readings can be used to guide clinicians with any further changes in hypertension medications.

10.1136/bmjopen-2017-016709.supp1Supplementary file 1

All participants will be invited to attend a 4-week follow-up appointment with the practice nurse. The main purpose of the visit is a clinical review of medication, including any adjustments required. Any changes in medication will be recorded on the concomitant medication log. Participants will be invited to attend further follow-up visits with a member of the trial team at the GP practice at 12 weeks, 6 months and 12 month following randomisation. Participant flow through the study is outlined in figure 1.

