#### Exploratory outcomes

change in fat mass from baseline to 12 weeks and from baseline to 6 monthschange in waist circumference from baseline to 3, 6 and 12 monthschange in triglyceride and high-density lipoprotein (HDL) cholesterol concentrations between baseline and 12 monthschange in fasting glucose and insulin concentrations and change in Homeostatic Model Assesment (HOMA)of insulin resistance (HOMA- IR), insulin sensitivity (HOMA-%S) and beta cell function (HOMA-%B) between baseline and 12 monthschange in systolic and diastolic blood pressure between baseline and 3 months and between baseline and 6 monthschange in QRISK between baseline and 12 monthschange in the quality of Life measured using the EQ-5D scale between baseline and 12 monthschange in obesity-related quality of life measured with the Obesity-Specific Quality of Life (OWLQOL) between baseline, 3, 6 and 12 monthsproportion of people continuing their weight loss attempt and following the prescribed programme at 4, 8 and 12 weeksthe number of weight control behaviours that participants are using assessed using the Oxford Food and Activity Behaviours (OxFAB) questionnaire^18^ at 3 and 6 monthsqualitative interviews with a subsample of participants at 6 and 12 monthsadverse event (AE) reports up to 12 weeks, the end of the weight loss intervention or 6 months for AEs known or presumed to be related to gallstones.

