### Trial Steering Committee

An independent Trial Steering Committee (TSC) will provide oversight of all matters relating to participant safety and data quality and value to the public. Due to the low risk nature of the DROPLET trial and that it is an open-label trial, the TSC also has the role of the Data Monitoring Committee, in addition to its role as the TSC. However, there are no early stopping rules, and all AEs are evaluated unblinded to allocation by the trial management group as well as the TSC.

The TSC includes an independent clinician, dietitian, statistician and two patient representatives. The TSC has reviewed the trial protocol, statistical analysis plan and the suitability of the proposed safety data to be collected. No interim analysis is planned for this trial due to the short recruitment period and low risk nature of the two dietary approaches.^11^ The trial may be subject to inspection and audit by the University of Oxford, under their remit as sponsor, the trial coordinating centre as the Sponsor's delegate and other regulatory bodies.

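### Late biliary-type events are recorded only if attributed to gallstones and only to 6 months, so capture may differ by arm and is short after late repeat dieting; the general AE window lacks one clear end

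*Protocol article*

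**What the plan says.** The Adverse events section sets two collection rules. The general rule covers "All serious and non-serious AEs that occur during the first 12 weeks of the study or until the termination of the weight loss programme", and these "will be recorded in participants who initiate one of the weight loss interventions". The second rule extends follow-up for one harm: "We will also record all AEs that are presumed to be or known to be related to gallstones up to 6 months". The Exploratory outcomes list repeats both limits, with AE reports running to 12 weeks, "the end of the weight loss intervention or 6 months for AEs known or presumed to be related to gallstones".

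Four other sections bear on these rules:

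- **Masking.** Design and setting states that participants, clinicians and part of the study team cannot be blinded. The Trial Steering Committee section adds that "all AEs are evaluated unblinded to allocation by the trial management group as well as the TSC".
- **Exposure in the diet arm.** Low-energy total diet replacement describes 8 weeks of total diet replacement, 4 weeks of food reintroduction, and a maintenance phase from week 12 to week 24 with appointments at weeks 16, 20 and 24. In that phase, participants who regain 1 kg or more are recommended to go back to total diet replacement for periods of at most 4 weeks. Consultations and products "will be free of charge for the first 24 weeks, after which the intervention will end". Continuing afterwards is allowed at the participant's own cost.
- **Comparator.** The nurse programme is offered for 12 weeks.
- **Study visits.** Participant flow schedules them "at 12 weeks, 6 months and 12 month following randomisation".

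**The concern.** Gallstone disease is the only harm that the article singles out for longer follow-up, and three features weaken what that follow-up can show.

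First, once the general window has closed, an event with no established diagnosis is recorded only if it is presumed to be gallstone-related. Where allocation is known, the same upper abdominal pain could be read as biliary more readily in a participant known to be losing weight fast. The diet arm also has three scheduled provider contacts after week 12 at which symptoms might come up. The nurse programme has none scheduled over that period.

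Second, the 6-month limit is counted in study time and takes no account of when a participant was last on total diet replacement. A late repeat period brings the exposure close to the end of collection.

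Third, the general window has two candidate closing points. Under one of them, the period of all-AE recording differs in length between the arms.

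The Adverse events section gives the reason this matters: many practitioners regard these programmes as poorly tolerated and unsuited to routine primary care. Data on the named harm that are incomplete, or gathered unevenly by arm, answer that doubt less well. An analysis plan written later cannot repair this, because events that were never collected cannot be analysed.

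**Working it through.** The article gives no figure on this point to reproduce. The sample size plays no part in it. The check is calendar arithmetic followed by a comparison of sections.

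**Inputs**

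- Gallstone collection closes at 6 months (Adverse events; Exploratory outcomes).
- Initial total diet replacement ends at week 8, and the provided intervention at week 24 (Low-energy total diet replacement).
- The weight loss phase is weeks 1 to 12 (Participant flow).
- The nurse programme lasts 12 weeks (Comparator).
- The last study visit is at 12 months (Participant flow).

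**Step 1: the window in weeks.** 6 months = 365.25 / 2 / 7 = 26.1 weeks.

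**Step 2: follow-up after exposure.** Tail = 26.1 minus the week in which the exposure ends, taking the programme to start on the day of randomisation.

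| Exposure ends | Tail (weeks) |
|---|---|
| Initial diet, week 8 | 26.1 − 8 = 18.1 |
| Weight loss phase, week 12 | 26.1 − 12 = 14.1 |
| Repeat ending week 16 | 26.1 − 16 = 10.1 |
| Repeat ending week 20 | 26.1 − 20 = 6.1 |
| Repeat ending week 24 | 26.1 − 24 = 2.1 |

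The short tail belongs to late repeats only.

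**Step 3: sensitivity to start date.** Study visits are timed from randomisation, and the article does not give the interval from randomisation to the first day of the diet. Assuming a delay of 1, 2 or 3 weeks, the tail after programme week 24 becomes 26.1 − 25 = 1.1, 26.1 − 26 = 0.1 and 26.1 − 27 = −0.9 weeks. With no delay, a 4-week repeat begun at week 24 and continued at own cost would end at week 28, which is 28 − 26.1 = 1.9 weeks after collection closes.

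**Step 4: follow-up not used.** Twelve months is 52.2 weeks, so 52.2 − 26.1 = 26.1 weeks, half of the follow-up, have no stated gallstone collection although a visit is held at the end of them.

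**Step 5: when the general window closes.** Two readings are open.

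- *Week 12 in both arms.* Participant flow supports this: participants on antihypertensives in the diet arm are "asked to record blood pressure once daily during the weight loss phase (weeks 1–12". The Exploratory outcomes wording can also be read as equating 12 weeks with the end of the weight loss intervention.
- *The end of each arm's programme.* The diet intervention ends at week 24 and the nurse programme at week 12. All AEs would then be recorded for 24 − 12 = 12 weeks longer in the diet arm. Attribution would decide entry only after week 24 in that arm, but from week 12 in the nurse arm.

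**Step 6: what attribution decides.** The trigger has two limbs, known and presumed. Known gallstone events are recorded in either arm to 6 months. Attribution matters only for events without an established diagnosis. For those, the article states one rule for both arms and does not say who applies it.

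**The case against.** The strongest case on the other side has five parts.

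- **The rule is the same in both arms and covers known events.** This stands. A reader might infer that late gallstone events count only if unmasked staff presume the cause, or that comparable events in the nurse arm are thrown away. The text supports neither. Much of any objective list, such as gallstone diagnoses, cholecystitis and cholecystectomy, would largely be captured already as known events. What remains is the undiagnosed margin.
- **Bias is not shown.** This also stands. The Trial Steering Committee section concerns how recorded AEs are evaluated, not who decides to record them, and only some of the study team are unmasked. The article gives no event rate and nothing that fixes a direction or size.
- **The 2-week figure is an extreme.** It applies to a participant who regains at least 1 kg and whose repeat ends at week 24. A repeat ending at week 16 leaves about 10 weeks, and a participant with no repeat has about 18 weeks after the initial diet. The plan sets no minimum tail that it then breaks.
- **An article condenses.** Case definitions and adjudication may sit in the full protocol, and the measurement schedule figure is not shown. Their absence here is therefore no finding. The trigger and the 6-month limit are different: both are stated, in two sections.
- **The consequence is limited.** AE reports are exploratory, and the Statistical analysis section describes no between-arm AE test. That lowers the priority, but does not make the missing events recoverable.

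**Conclusion.** The point holds in a limited form, as a cheap improvement that should be made. After the general window, undiagnosed biliary-type events depend on attribution in an open-label trial, and contact schedules differ after week 12, so ascertainment may differ by arm. Collection stops as little as about 2 weeks after a late repeat of total diet replacement, against about 18 weeks after the initial diet and 14 weeks after week 12. The 2-week figure assumes a start on the day of randomisation and a repeat ending at week 24. With an assumed delay of 1 to 3 weeks it runs from 1.1 down to −0.9.

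Separately, the sections leave open whether general AE recording closes at week 12 or with each arm's programme, a possible 12-week difference between arms.

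A reader might conclude that the gallstone comparison is biased, or that the trial cannot speak credibly to gallstone risk. The document does not support that: it shows an opening for differential and incomplete ascertainment, not its presence, direction or size. The primary outcome is not affected.

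**What to change.** 1. In Adverse events and Exploratory outcomes, replace the attribution trigger with a short list of biliary-type events, recorded in both arms whatever the presumed cause. Examples are a gallstone diagnosis, cholecystitis, pancreatitis, cholecystectomy, and hospital attendance for upper abdominal pain.
2. Ask about these events at the existing 6- and 12-month visits, and run the window to 12 months.
3. Reconcile Participant flow, Low-energy total diet replacement, Comparator, Exploratory outcomes and Adverse events so that general AE recording closes at one stated time point, the same in both arms.

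These are changes to data collection and wording. They add no visit and leave both programmes as they are. The cost is a few extra questions at visits already planned, and some non-biliary events to sort.
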